### Dropout of participants

• Misdiagnosis

• Using forbidden drugs or treatments in the course of the trial

• Taking no medication during the trial

• No evaluable records after medication

### The whole study will be terminated if any of the following occurs

• Poor curative effect is found during the study

• Significant deviation from the protocol

• Flawed protocol

• The sponsors decide to terminate the trial due to management or funding problems

• At the decision of the pharmaceutical supervisory and administrative department

### Concomitant treatments and forbidden drugs

Usage of any other Western medication or Chinese medicines that have similar effects to SQTX Granule, or may affect the analysis of the final results, is strictly prohibited. Medications used to control other conditions of the participants, such as hypertensive or diabetic medications, are allowed. The dosage, duration and name of any concomitant treatment or medication must be recorded carefully in the CRFs.

### Test drugs

The test drugs are SQTX Granule and placebo, which are indistinguishable from the actual medication. The placebo has the same shape, size, taste, colour, package and Lot number.

### Intervention

Patients are administered SQTX Granule or placebo in one bag (0.5 g per bag) dissolved in warm water three times daily for 28 days. The follow-up visits last for one week after the treatment. The measurements that need to be performed at each visit are listed in Figure 
2.

**Figure 2 F2:**
[figure not shown]
**Study schedule for patients.** After the enrolment and allocation, participants will receive the administration for four weeks and a follow-up of eight weeks. The time-points of assessment are shown in the schedule.

### Outcome assessment

#### Primary outcome

• Scores of IBS-quality of life rating scale (IBS-QOL) rating scale
[21]

• Scores of IBS-symptom severity scale (IBS-SSS) rating scale
[22]

### Secondary outcome

• The symptom score system is introduced to quantify the degree of abdominal pain, diarrhea, stool consistency and other concomitant symptoms as shown in Figure 
3, following the Guidelines for Clinical Research of New Chinese Medicine
[20].

**Figure 3 F3:**
[figure not shown]
**Symptom score system.** As a secondary outcome, a Traditional Chinese medicine (TCM) symptom score system is introduced into this protocol.

• The treatment efficacy evaluation system is introduced to evaluate the improvement of symptoms using the percentage of symptom score reduction (PSSR). The PSSR for a patient after treatment is calculated according to the following formula:

$$\begin{array}{ll} \;\text{PSSR} & =\left(\frac{\text{Symptom}\;\text{score}\;\text{at}\;\text{Day}\;0‒\text{Symptom}\;\text{score}\;\text{at}\;\text{Day}\;28}{\text{Symptom}\;\text{score}\;\text{at}\;\text{Day}\;0}\right)\\ & \;\times 100\% \end{array}$$

Full recovery: PSSR ≥ 90%, Good recovery: 90% > PSSR ≥ 70%, Modest recovery: 70% > PSSR ≥ 30%, No recovery: PSSR < 30%.

• Decreasing and disappearing time of abdominal pain and diarrhea:

  Decreasing time = (The day pain/diarrhea decrease) - Day 1

  Disappearing time = (The day pain/diarrhea disappear) - Day 1

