### Western medicine diagnostic criteria for IBS-D

Diagnosis of IBS-D is established according to the Rome III criteria
[11,12], mode listed in Table 
2.

**Table 2 T2:** Mode of irritable bowel syndrome (IBS)

**Question**	**Score**
A) In the last 3 months, how often did you have hard or lumpy stools?	0 Never or rarely
	1 Sometimes
	2 Often
	3 Most of the time
	4 Always
B) In the last 3 months, how often did you have loose, mushy or watery stools?	0 Never or rarely
	1 Sometimes
	2 Often
	3 Most of the time
	4 Always
**Mode**	**Definition**
IBS-C	A > 0 and B = 0
IBS-D	A = 0 and B > 0
IBS-M	A > 0 and B > 0
IBS-U	A = 0 and B = 0

Diagnostic criteria*:

Recurrent abdominal pain or discomfort** at least three days/month in the last three months associated with two or more of the following:

1. Improvement with defecation

2. Onset associated with a change in frequency of stool

3. Onset associated with a change in form (appearance) of stool

*Criteria fulfilled for the last three months with symptom onset at least three months prior to diagnosis

**‘Discomfort’ means an uncomfortable sensation not described as pain.

In pathophysiology research and clinical trials, a pain/discomfort frequency of at least two days a week during the screening evaluation is recommended for subject eligibility.

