### Other criteria

Withdrawal of participants:

• Patients are determined as requiring withdrawal based on disease progression, allergic reactions, serious adverse events, or poor efficacy

• Serious complications

• Unblinding individuals for any reasons

• Voluntarily quitting

• Unable to complete the scheduled follow-up

Reasons for withdrawing patients would be noted in Case Report Forms (CRFs), and the last data would be included in data analysis.

Note: 1) Patients cured in a course of treatment are not regarded as cases for withdrawal.

2) Patients withdrawn due to poor efficacy after a half course of treatment (14 days) are regarded as not recovered but not withdrawn, and they would be included in the Full Analysis Set (FAS) and the Per Protocol Set (PPS).

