### Data analysis

Statistical analysis will be conducted based on an intention-to-treat (ITT) principle. All subjects who were treated with at least one dose of the study drug and had at least one clinical observation after starting the treatment comprise FAS. All treated subjects without any major protocol deviations comprise PPS. The statistical analysis will be performed using the SAS 8.1 software (SAS, Cary, NC, USA). The statistical significance is defined as a two-sided *P*-value of < 0.05. Baseline differences among the groups will be assessed with the use of the one-factor analysis of variance or the Mann-Whitney *U-*test for measurement data and the χ^2^ test or the Wilcoxon test for enumeration data. For categorical variables, a χ^2^ test or Fisher’s exact test will be used. The changes from baseline to endpoint of treatment in scores will be assessed with the use of a paired *t*-test for measurement data and a signed rank test for enumeration data. Comparisons between groups will be conducted by using an analysis of variance (ANOVA) and a rank test.

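### Times to decrease and disappearance of pain and diarrhea have no value for patients without the event, and the stated ANOVA and unspecified rank test come with no rule for including them

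*Protocol article*

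**What the plan says.** The Secondary outcome section of the protocol article defines two times for abdominal pain and diarrhea: "Decreasing time = (The day pain/diarrhea decrease) - Day 1" and "Disappearing time = (The day pain/diarrhea disappear) - Day 1". It gives no value, censoring day or rank for a patient in whom the event does not occur.

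The Data analysis section has one general sentence on group comparisons: "Comparisons between groups will be conducted by using an analysis of variance (ANOVA) and a rank test". No Kaplan-Meier, log-rank or Cox analysis is named. The same section states: "Statistical analysis will be conducted based on an intention-to-treat (ITT) principle".

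The article expects some patients not to improve. Its efficacy categories include "No recovery: PSSR < 30"%. Under Other criteria, "Patients withdrawn due to poor efficacy after a half course of treatment (14 days) are regarded as not recovered but not withdrawn", and these patients stay in both the full analysis set and the per-protocol set. For other withdrawals, "the last data would be included in data analysis".

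**The concern.** The outcome definition and the stated test do not fit together. The definition yields a number only when the event happens. ANOVA needs a number for every patient it includes. Followed as written, the analysis either leaves out everyone without the event or needs a value the article does not supply.

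If they are left out, the comparison is between active patients who improved and placebo patients who improved. Randomisation does not protect that comparison. A drug that helps more patients, but at the same pace among those helped, would show no difference. A drug whose additional responders improve late would look slower than placebo.

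**Working it through.** **Is there a figure to reproduce?** No. The article gives no event rate, median time or power for these outcomes, so the check is a reading of the text followed by an illustration.

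**Does any rule fill the gap?** The last-data rule for withdrawals supplies a last score, not a day for an event that never happened. The not-recovered rule for poor-efficacy withdrawals supplies a status, not a day. Neither gives these patients a time.

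**Inputs to the illustration.** From the article: 330 and 110 patients, 28 days of treatment, two-sided 0.05. Assumed: 50% and 35% have the event by Day 28. These figures are borrowed from the response rates in the sample size section, which are not event rates for these outcomes.

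**Patients with a value.** Active: 330 × 0.50 = 165. Placebo: 110 × 0.35 = 38.5, about 38. Without a value: 165 active and 110 × 0.65 = 71.5, about 72, placebo.

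**Why timing among improvers says little.** With a constant hazard, and 27 days from Day 1 to Day 28, λ = −ln(1 − p)/27.
- Active: 0.6931/27 = 0.02567.
- Placebo: 0.4308/27 = 0.01595.
- The hazard ratio is 0.6931/0.4308 = 1.61, a clear benefit.

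The mean time among those with the event is 1/λ − 27(1 − p)/p.
- Active: 38.95 − 27.00 = 11.95 days.
- Placebo: 62.68 − 50.14 = 12.54 days.

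The difference is about 0.6 days. Rounding up to whole days adds about half a day to each arm, which agrees with the simulated means of 12.5 and 13.0.

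**Simulation.** Share of 1,000 runs with p < 0.05, 330 versus 110 patients:

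| Scenario | Improvers, ANOVA | Improvers, rank test | All patients, non-events ranked last | Log-rank |
|---|---|---|---|---|
| 50% vs 35%, constant hazards | 7% | 7% | 79% | 78% |
| 50% vs 35%, same timing among improvers | 4% | 4% | 74% | 77% |
| 50% vs 35%, extra active responders improve late | 46% | 47% | 51% | 67% |
| 35% in both arms | 4% | 4% | 5% | 5% |

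In the late-responder scenario the mean among improvers is 16.6 days on active and 13.9 on placebo, so most of the 46-47% points against a drug that works. A separate run of 3,000 replicates of the constant-hazard case, with a 28-day horizon, gave 7% for both tests among improvers and 79% for log-rank.

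**Range over event rates.** With constant hazards, power of the t-test among improvers is 7% at 50/35, 14% at 70/55, 34% at 90/80 and 68% at 95/85. At 95/85 the all-patient rank test has 93%.

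**The case against.** The strongest reply is that the article never says non-improvers are excluded. It states intention to treat, keeps poor-efficacy withdrawals in both analysis sets, and does not tie a test to the time outcomes; the ANOVA and rank-test sentence is a general one. How non-events are coded could sit in a full protocol or analysis plan that is not shown. This stands in part: exclusion is an inference. But the article does state the formula and the methods, and for ANOVA the pair does not work without an added rule.

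Four stronger readings are tempting, and the text does not support them.
- **That none of the listed tests can handle these patients.** An ordinary rank test can, if patients without the event are ranked last; in the constant-hazard case it matches log-rank (79% against 78%). ANOVA has no such option.
- **That the protocol's own rates show half or more of patients without a value.** The 0.50 and 0.35 are an undefined response rate. A mere decrease could be much more common, and the loss is then smaller.
- **That information on how many patients improve is lost to the trial.** The efficacy categories based on percentage score reduction still capture it, and the primary outcomes, IBS-QOL and IBS-SSS, are untouched.
- **That one pain-free day would count as disappearance.** The entry criterion of pain "at least three days/month in the last three months" would allow 27 of 30 days, 90%, to be pain-free. The same section, however, recommends at least two days a week for clinical trials, which allows 5 of 7, about 71%. Both are minimum frequencies and concern pain or discomfort, not diarrhea. No single-day rule is stated, and the scoring and schedule figures are not shown.

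**Conclusion.** The point holds in a limited form. The two time outcomes have no value for patients without the event, and one of the two stated methods, ANOVA, cannot include such patients unless a value is invented. The other, the rank test, can include them only under a rule that the article does not give. Restricting the comparison to patients with the event would select on a post-randomisation outcome and break the stated intention-to-treat principle.

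The direction of the problem does not depend on the simulation, but its size does. About 7% against 78-79% power rests on assumed event rates of 50% and 35%, constant hazards and no loss to follow-up. At 95% and 85% the contrast is 68% against 93%. Only secondary outcomes are affected, so this should be corrected before unblinding but does not threaten the primary analysis.

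**What to change.** Drop ANOVA for decreasing time and disappearing time. Analyse all patients in the full analysis set as time-to-event: Kaplan-Meier curves, a log-rank test and a Cox hazard ratio, with patients without the event censored at the end of the 28-day treatment. A rank test with non-events ranked last is an acceptable alternative, though it had less power than log-rank when the extra responders improved late (51% against 67%).

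Keep patients withdrawn for poor efficacy, whom the article already counts as not recovered, as event-free to Day 28. Censoring them at withdrawal would be informative, because they left for lack of improvement.

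The cost is changed analysis wording and standard SAS procedures. Defining disappearance as a sustained symptom-free run is optional. It depends on symptoms being recorded daily, which the sponsor should confirm.

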### Safety outcome

A routine blood test, routine urine test, routine stool test, faecal occult blood test, urine pregnancy test (women only), liver function test, renal function test and an electrocardiogram are administered for safety outcomes, which are monitored both before and after treatment.

### Data management

After review by clinical inspectors, completed CRFs will be sent to a specified statistics centre, and data entry and management is completed by two individual data administrators to ensure the accuracy of the data. To ensure the database is created correctly after blind review, data will be locked by the clinical research leader, the sponsor and the statistical analyst, so that no changes are allowed to the locked data.

### Adverse events

Adverse events will be recorded and graded in detail throughout the study. When a severe adverse event occurs, participants will be provided with every necessary treatment, and the event must be reported to the leader of the trial, ethics committees, sponsors and CFDA within 24 hours.

### Data analysis

Statistical analysis will be conducted based on an intention-to-treat (ITT) principle. All subjects who were treated with at least one dose of the study drug and had at least one clinical observation after starting the treatment comprise FAS. All treated subjects without any major protocol deviations comprise PPS. The statistical analysis will be performed using the SAS 8.1 software (SAS, Cary, NC, USA). The statistical significance is defined as a two-sided *P*-value of < 0.05. Baseline differences among the groups will be assessed with the use of the one-factor analysis of variance or the Mann-Whitney *U-*test for measurement data and the χ^2^ test or the Wilcoxon test for enumeration data. For categorical variables, a χ^2^ test or Fisher’s exact test will be used. The changes from baseline to endpoint of treatment in scores will be assessed with the use of a paired *t*-test for measurement data and a signed rank test for enumeration data. Comparisons between groups will be conducted by using an analysis of variance (ANOVA) and a rank test.

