**Methods/Design:**

A randomised, double-blinded, placebo-controlled, multi-centre, superiority clinical trial to evaluate the efficacy and safety of SQTX Granule is proposed. Eligible patients (Rome III) with IBD-S will be randomly assigned into SQTX Granule group and the placebo group. Patients will receive a 28-day treatment and a 2-month follow-up. The primary outcome measures include the scores of IBS-quality of life (IBS-QOL) rating scale and IBS-symptom severity scale (IBS-SSS) rating scale. The secondary outcome measures include the improvement of symptom scores, and the duration of abdominal pain and diarrhea.

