### Recruitment

A total of 440 Chinese patients who fulfill the screening criteria will be recruited at eight large comprehensive hospitals in China: 1) West China Hospital of Sichuan University, 2) Affiliated Hospital of Chengdu University of TCM, 3) The First Affiliated Hospital of Heilongjiang University Of Chinese Medicine, 4) Affiliated Hospital of Jiangxi University of TCM, 5) Shanxi Provincial Hospital of TCM, 6) The First Affiliated Hospital of Guangxi University of Chinese Medicine, 7) Gansu Provincial Hospital of TCM and 8) Affiliated Hospital of Changchun University of Chinese Medicine. Each centre will recruit 55 patients through posters in local hospitals.

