### Randomisation

With a stratified block randomisation method, a 440-case randomisation arrangement was carried out by an independent statistician according to the sequence generated with SAS software; this lists a serial number from 001 to 440 corresponding to consecutive allocation (with a randomisation scheme). Each centre receives consecutively coded drugs. All of the drugs provided by the pharmaceutical company will be numbered with a label according to the randomisation schedule.

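### The stated between-group comparison names no baseline covariate or randomisation stratum; ANCOVA with both would be more precise at no cost

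*Protocol article*

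**What the plan says.** The protocol article names two scores as primary: "The primary outcome measures include the scores of IBS-quality of life (IBS-QOL) rating scale and IBS-symptom severity scale (IBS-SSS) rating scale".

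The between-group method is one sentence under Data analysis: "Comparisons between groups will be conducted by using an analysis of variance (ANOVA) and a rank test". It does not say whether final scores or changes are compared, and it lists no model terms.

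The same section uses baseline values in two other places. One is a check of comparability: "Baseline differences among the groups will be assessed with the use of the one-factor analysis of variance or the Mann-Whitney" test, with other tests for enumeration data. The other is a within-group test: "The changes from baseline to endpoint of treatment in scores will be assessed with the use of a paired" *t*-test, or a signed rank test for enumeration data.

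Under Randomisation the article reports: "With a stratified block randomisation method, a 440-case randomisation arrangement was carried out by an independent statistician". The stratification factor is not given. Two statements point to centre: "Each centre receives consecutively coded drugs" under Randomisation, and "Each centre will recruit 55 patients through posters in local hospitals" under Recruitment, with eight centres listed.

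**The concern.** The trial has two sources of precision that it has already paid for: a baseline value of each primary score, and a stratified allocation. The stated comparison between groups calls on neither. Of the two uses of baseline in the section, the comparability test does not sharpen the treatment estimate, and the paired tests look within one arm and give no treatment contrast.

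What is at stake is precision: a wider confidence interval for the treatment difference than the same 440 patients could give. The estimate would not be biased. A test that leaves out the strata used in the allocation tends to have a standard error that is somewhat too large, so it errs on the cautious side.

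**Working it through.** **Inputs from the documents.** Allocation 330:110 (Sample size calculation); two-sided 5% level (Data analysis); two continuous primary scores (Primary outcome); stratified allocation with unnamed factor (Randomisation). The plan gives no variance, score difference or correlation for IBS-QOL or IBS-SSS, so it has no figure of its own to reproduce on this point.

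**Assumptions.** Correlation r between baseline and end-of-treatment score from 0.3 to 0.7; the same standard deviation σ at both times; the same baseline slope in both arms. The few degrees of freedom spent on covariates are ignored.

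**Step 1: baseline.** The variance of the treatment difference is the per-patient variance times (1/330 + 1/110). That factor is common to all three methods and cancels. The per-patient variances are:

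- ANOVA on final scores: σ²
- ANOVA on change: σ² + σ² − 2rσ² = 2(1 − r)σ²
- ANCOVA on baseline: (1 − r²)σ²

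The ratio of ANCOVA to final-score ANOVA is 1 − r². The ratio of ANCOVA to change-score ANOVA is (1 − r²)/[2(1 − r)] = (1 + r)/2. Both are below 1 for every r between 0 and 1.

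| Assumed r | 1 − r² | Reduction vs final scores | (1 + r)/2 | Reduction vs change |
|---|---|---|---|---|
| 0.3 | 0.91 | 9% | 0.65 | 35% |
| 0.5 | 0.75 | 25% | 0.75 | 25% |
| 0.7 | 0.51 | 49% | 0.85 | 15% |

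The last final-score entry is 1 − 0.51 = 0.49; the more exact statement of the range against final scores is therefore that the variance factor runs from 0.91 down to 0.51. At r = 0.5, 1/0.75 = 1.33, so the gain is worth about a third more patients under either reading.

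**Step 2: strata.** If the stratum explains a share p of the outcome variance, a test that leaves it out has a standard error too large by about 1/√(1 − p). Its actual two-sided error rate is then about 2[1 − Φ(1.96/√(1 − p))]. The documents give no p; for assumed values:

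- p = 0.01: 4.9%
- p = 0.05: 4.4%
- p = 0.10: 3.9%

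The error rate stays below the nominal 5% throughout. The precision lost is about p itself.

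**The case against.** The strongest objection is that a journal article condenses the full plan, that model terms usually sit in the SAP, and that silence is not exclusion. In part this stands: an unseen SAP may already specify adjustment. But the article does not leave the method open. It names one, and the named method can be improved. If the SAP differs, the sentence should be brought into line with it.

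A reader might also infer stronger points, which the documents do not support:

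- *The efficacy test is a one-way, unadjusted ANOVA.* The one-factor label is attached only to the baseline comparison. A centre factor in the efficacy ANOVA is not ruled out.
- *Baseline is ignored.* The sentence just before the one on group comparisons concerns changes from baseline. If the ANOVA is on changes, baseline is used, but inefficiently. The symptom-score reduction in the secondary outcomes is also built on the Day 0 value.
- *Centre was the stratum.* This is likely but not stated.
- *Two competing tests allow the better p-value to be chosen.* The section pairs its tests by data type, measurement against enumeration. The ANOVA and the rank test may follow that pattern and so never compete on a primary score. The wording is loose, but competition between tests is not established.
- *The trial's power would rise from one stated figure to another.* The sample size rests on a binary response rate. Power on the primary scores cannot be derived from the documents, so none is quoted here.
- *The analysis is invalid.* Comparing randomised groups without these covariates is unbiased, and omitting the strata makes the test cautious.

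**Conclusion.** The point holds as one of efficiency. The stated comparison names neither the baseline score nor the randomisation stratum, and an ANCOVA with both would be more precise whether the ANOVA is meant for final scores or for changes. For assumed r of 0.3 to 0.7 the variance factor is 0.91 to 0.51 against final scores and 0.65 to 0.85 against changes, and 0.75 for both at r = 0.5. The direction follows from the algebra under the stated assumptions of equal standard deviations and a common slope. The size depends on an r that the documents do not give. The effect of the strata is small and conservative over the range examined. This is a free improvement, and it does not call the validity of the trial's comparison into question.

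**What to change.** Replace the sentence on group comparisons under Data analysis, and align any SAP, along these lines:

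> For each primary score (IBS-SSS and IBS-QOL), the deciding analysis is an ANCOVA of the end-of-treatment score on the FAS with treatment, baseline score and the randomisation stratum, reported as adjusted mean difference with 95% confidence interval. A stratified rank-based test is a sensitivity analysis for these scores. Ordinal outcomes, such as the categories of symptom-score reduction, are compared with a rank-based test stratified in the same way. Paired within-group tests are descriptive only.

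Name the stratification factor that was actually used and enter that factor in the model.

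Settle the wording before the first-level unblinding. The Blinding section opens the A/B code before the analysis, and with 330 against 110 patients the group sizes alone would show which group is which.

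The cost is a change of text. No new data, visits or patients are needed, and recruitment was still under way when the article was submitted (Trial status).

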### Sample size calculation

According to the results of Phase II clinical trial, the response rates of SQTX Granule and placebo were 0.51 and 0.33, respectively. Assuming the response rates for TCM and placebo were 0.5 and 0.35, the sample size was calculated under the setting of alpha = 0.05 and beta = 0.80. Taking into account a drop-out of 15%, the sample size needs to be 150 cases for each group. A total of 440 patients will be recruited in this trial, including 330 cases for the SQTX Granule group and 110 cases for the placebo group in a 3:1 ratio.

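### With 3:1 allocation, ordinary ANOVA loses the protection against unequal SDs that 1:1 would give; an unequal-variance comparison restores it at almost no cost

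*Protocol article*

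**What the plan says.** The Data analysis section of the protocol article gives the between-group method in one sentence: "Comparisons between groups will be conducted by using an analysis of variance (ANOVA) and a rank test". It sets the level in the same paragraph, where "statistical significance is defined as a two-sided" P-value below 0.05. The Sample size calculation section describes the total of 440 as "including 330 cases for the SQTX Granule group and 110 cases for the placebo group in a 3:1 ratio". The primary outcomes are two scores, IBS-QOL and IBS-SSS.

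The article does not say whether the ANOVA pools the variance, which score is compared by ANOVA and which by the rank test, or what SD is expected for either score in either arm. It plans no confidence interval. Under Blinding, patients are disclosed as group A or group B before the statistical analysis, and the meaning of the two letters is disclosed later.

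**The concern.** ANOVA named without qualification ordinarily means one residual variance common to both arms. With equal arms this assumption is harmless for a two-group comparison, because the pooled standard error of the difference is right even if the SDs differ. With three SQTX patients to each placebo patient it is not harmless. About three-quarters of the pooled variance estimate comes from the SQTX arm. When the SDs are similar, about three-quarters of the true sampling variance of the difference comes from the placebo arm. If the SDs differ, the wrong arm dominates the error estimate.

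Unequal spread is plausible in either direction. Patients who improve strongly may bunch at the good end of a bounded scale, which would make SQTX scores less variable and the standard error too small. Patients may also respond to the drug to different degrees, which would make SQTX scores more variable, the standard error too large and the power lower. Adding baseline covariates or strata does not remove the problem while the residual variance is still pooled.

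**Working it through.** **Inputs.** Arm sizes 330 and 110, dropout 15% (Sample size calculation); two-sided 0.05 (Data analysis). Evaluable patients: 330 × 0.85 = 280.5 and 110 × 0.85 = 93.5, taken as 280 and 94. *Assumption:* the article gives no SDs, so the placebo/SQTX SD ratio r is varied, with the SQTX SD set to 1.

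**Plan's own figure.** There is none for this comparison. The only computed figure, 150 per group, rests on response rates and contains no SD, so it has no bearing here.

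**Formulas.**
- Pooled variance = (279 × 1 + 93 × r²)/372 = 0.75 + 0.25r²
- Assumed variance of the difference = (0.75 + 0.25r²) × (1/280 + 1/94) = (0.75 + 0.25r²) × 0.01421
- True variance of the difference = 1/280 + r²/94 = 0.003571 + 0.010638r²
- SE ratio R = √(true/assumed)
- Actual level for equal means = 2 × [1 − Φ(1.96/R)]

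| r (placebo/SQTX) | Assumed variance | True variance | R | Actual level |
|---|---|---|---|---|
| 0.80 | 0.01293 | 0.01038 | 0.896 | 2.9% |
| 0.90 | 0.01353 | 0.01219 | 0.949 | 3.9% |
| 1.00 | 0.01421 | 0.01421 | 1.000 | 5.0% |
| 1.10 | 0.01496 | 0.01644 | 1.049 | 6.2% |
| 1.25 | 0.01621 | 0.02019 | 1.116 | 7.9% |

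The coverage of a nominal 95% interval is 100% minus the level: 97.1% at r = 0.80 and 92.1% at r = 1.25.

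**Same total at 1:1 (187 v 187).** Assumed variance = [(1 + r²)/2] × (2/187) = (1 + r²)/187, which equals the true variance for every r. The level is 5.0% throughout.

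**Simulation check.** With 400,000 normal trials per setting at 281 v 94, the pooled test rejects in 2.9% at r = 0.80 and 7.9% at r = 1.25. The Welch test stays at about 5.0% at every ratio tried. Without dropout (330 v 110) the pooled results are nearly the same: 2.8% and 7.9%.

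**Rank test.** Mann-Whitney at 330 v 110 (4,000 trials per setting, so a Monte Carlo error of about 0.3 points) gives 4.6% at r = 0.80 and 6.1% at r = 1.25. At r of about 0.67 and 1.5 it gives 2.8% and 8.7%. It shares the sensitivity, to a smaller degree.

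**Power lost if SQTX scores are more variable (r = 0.80).** The true SE is √0.01038 = 0.1019. A comparison with the correct SE has 80% power at a difference of (1.96 + 0.84) × 0.1019 = 0.285. The pooled test needs 1.96 × √0.01293 = 0.223 to reject, so its power is Φ[(0.285 − 0.223)/0.1019] = Φ(0.61), or about 73%.

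**Price of Welch if the SDs are equal.** At a standardised difference of 0.335, the noncentrality is 0.335/√0.01421 = 2.81. Power is 80.0% with 372 degrees of freedom (pooled) and 79.8% with about 160 (Welch). A simulation of 20,000 trials gave 79.6% and 79.4%.

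**The case against.** The strongest reply is that the article contains no error. It never says the variance is pooled, the variance option behind a named test is commonly left to the analysis plan, and that plan is not shown. This stands in part. Nothing in the article is contradicted or miscalculated, and a plan not shown may already specify an unequal-variance analysis. However, the article does name a method, its ordinary meaning pools the variance, and it fixes an allocation with which that method fits poorly. Nothing else in the article repairs this, and the rank test is not a full remedy.

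Several stronger readings are tempting, and the documents do not support them:

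- *That the trial's false-positive rate is inflated.* If the drug does nothing to any patient, randomisation gives both arms the same distribution and the 5% level holds. The altered levels require equal means with unequal spread. If bunching at the good end is what makes the spreads differ, the means differ too, so rejection is not a false positive; what remains is interval coverage.
- *That the effect is large.* A ratio of 1.50 would give 10.7%, but nothing points to such a ratio. As an illustration, shift a normal score by 0.385 SD (the normal-scale gap between the assumed response rates of 0.50 and 0.35, which the article does not define on either primary score) and put a floor 0.5 to 1.5 SD below the placebo mean. The ratios are then only about 1.06 to 1.20, with coverage of about 94.3% to 92.7%. The harshest of these floors puts 31% of placebo and 45% of SQTX patients at the best possible score.
- *That the test is too liberal.* The direction is unknown; if change scores vary more under SQTX, it is conservative.
- *That both primary scores rest on ANOVA, or that planned intervals are wrong.* The article assigns neither test to a score and plans no interval.

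**Conclusion.** The point holds as a conditional one of optional priority. With ordinary ANOVA and 330 v 110, the test of equal means is exposed to unequal SDs in a way that 1:1 would not be. The effect is small for placebo/SQTX ratios of 0.9 to 1.1 and becomes material at about 0.8 or 1.25. At 0.8 the practical loss is power. At 1.25 it is a test of equal means, and any reported interval, that is too optimistic.

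This rests on three assumptions: ANOVA is meant in its pooled form, at least one primary score is compared by it, and the SDs differ. The article confirms none of the three. The point is worth making because the remedy costs almost nothing, not because the plan is shown to be wrong.

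**What to change.** Add one sentence to the Data analysis section: where IBS-QOL and IBS-SSS are compared between groups by ANOVA, the comparison will not assume equal variances. Either the Welch test and its interval, or the same linear model with arm-specific residual variances or HC3 standard errors, would do. Use the same standard errors in any covariate-adjusted version. If an existing analysis plan already says this, only the wording needs aligning.

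Settle it before the group A/B codes are disclosed. With 330 v 110, group size alone shows which letter is placebo, so a choice between variance options made after that step would in effect be unblinded.

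The cost is one sentence and one software option, with no extra patients or data, and about 0.2 to 0.4 points of power if the SDs turn out equal.
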